### Setting and participants

Participants over 18 years of age will be recruited from IUHVR. During the baseline visit, participants will be assessed and evaluated for eligibility, and informed written consent will be signed. Eligible participants will be allocated to the CYT treatment and will be followed up for an entire year from treatment initiation.

#### Inclusion criteria

The inclusion criteria are: adults ≥18 years old admitted to IUHVR participating wards with a history of smoking and interested in quitting. They must also be willing to utilize CYT pharmacotherapy, be available for a 12-month follow-up after treatment begins, and be able to provide written informed consent.

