### Study design

This study is a monocentric, observational prospective investigation involving smoking patients admitted to IUHVR and treated with CYT for smoking cessation.

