### Participant recruitment

Participating ward staff will be used to screen for and determine eligible participants, by physicians trained in the study by the principal investigator (PI) or sub-investigators (Sub-I), such as addiction medicine physicians (AMPs) or CM. Once potential participants are identified, ward staff will refer all current smokers interested in quitting smoking to the CM. Each patient’s eligibility for the study will be determined by the AMPs in collaboration with the CM, taking into account the patient’s current medical status and any contraindications to the usage of CYT.

The CM will then approach eligible patients, describe the CITOSP trial’s details to each potential participant, and answer any questions. If patients are willing to participate, prior to completing the baseline interview, written informed consent will be obtained.

Each participant will receive an anonymized study code at the baseline interview, and baseline data will be collected. This data will include general demographics such as age, gender, highest level of education, and current job position. Detailed medical histories will be considered, including medical conditions, current and remote anamnesis, and concomitant medications. Additionally, information on the participant’s smoking habits will be reviewed, such as age at smoking onset, cigarettes smoked per day, and previous attempts at quitting. Furthermore, the level of cigarette dependence assessed using the Fagerström Test for Cigarette Dependence (FTND) Questionnaire will be collected. The FTND is a validated and widely used questionnaire consisting of six items that measure the degree of nicotine dependence in tobacco smokers. The FTND yields a final total score ranging from 0 to 10. The patient’s physical nicotine dependence is closely related to the FTDN score. Scores from 0 to 2 indicate very low nicotine addiction; scores 3 and 4 indicate low nicotine addiction; a score of 5 indicates an average nicotine addiction; scores 6 and 7 indicate high nicotine addiction; and scores from 8 to 10 indicate very high addiction (32).

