The decision concerning the patient’s inclusion in the study will ultimately be made by the AMPs and the CM based on the predefined inclusion and exclusion criteria. Any participant who meets the exclusion criteria will not be recruited. Following the collection of baseline data, the AMPs and the CM will then give CYT, prepared by IUHVR’s HPs, to the participants and provide detailed counseling. In case of discharge, CYT will be provided to the patients to continue the therapy at home. CYT will be provided throughout the treatment duration according to the West dosing schedule (25 days, 101 capsules). In the case of patients with chronic kidney failure (stage IV or V), a reduced dosage schedule will be followed, providing 57 capsules.

On the first day of therapy, all participants will be instructed to abstain from smoking and to quit completely (quit day, QD).

Instructions about the West dosage schedule, common CYT ADRs, and emergency contact information will be given to participants by the CM. Finally, a study diary will be provided to support participants to help ensure proper intake of CYT.

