**Figure 1 fig1:**
[figure not shown]
Study protocol timeline. QD, quit day.

After the baseline visit, two visits (visit 1 at day 7 and visit 2 at the end of treatment, day 25) and three follow-ups (visit 3 at 3 months, visit 4 at 6 months, and visit 5 at 12 months) will be conducted (see Table 1). Visits 1, 2, and 3 will be conducted face-to-face. The last two visits (visits 4 and 5) will be conducted via telephone.

**Table 1 tab1:** Protocol timeline procedure of visits and follow-up for patients enrolled in the CITOSP trial.

Procedure	Visit 0	QD*	Visit 1	Visit 2^§^	Visit 3	Visit 4	Visit 5
Informed consent	√						
Inclusion/exclusion criteria	√						
Demographic characteristics	√						
Clinical history	√						
Smoking history and status	√						
Cytisine treatment		√	√	√			
Adverse events			√	√	√	√	√
Adverse drug reactions			√	√	√	√	√
Self-reported abstinence (PPA)			√	√	√	√	√
Biochemically verified abstinence (exhaled CO)			√	√^#^	√^#^		

QD, quit day.

PPA, point prevalence abstinence.

CO, carbon monoxide.

^#^Only if the visit is in person.

*First day of treatment. ^§^Stop treatment.

Each control visit resulted in the collection of the following records:

Visit 0 (baseline visit): informed consent dated and signed, participant identification code, and socio-demographic characteristics of the participant (age, sex, education, and occupation). Smoking history: age at which cigarettes were first smoked and efforts to quit smoking (number of times, date of last attempt, and use of some drugs to quit smoking). Smoking Status: average amount of cigarettes smoked in the last month, average cigarettes for the year, the score obtained in the FTND test, and use of other forms of nicotine delivery (for example, e-cigarettes). Clinical history: pathologies and ongoing pharmacological treatments. Integrated therapeutic: This statement outlines the non-pharmacological approaches used in the study to help patients, including counseling, cognitive-behavioral education, lifestyle changes, and the possible use of smoking cessation tools.

QD (first day of abstinence): start of integrated therapeutic plan with CYT.

Visit 1 (7^th^ from QD): continuation of the integrated therapeutic plan with CYT, evaluation of AEs, evaluation of ADRs, evaluation of PPA, number of cigarettes smoked (in case of quit failure), and exhaled CO.

Visit 2 (25^th^ day from QD): end of treatment with CYT, evaluation of AEs, evaluation of ADRs, evaluation of PPA, and exhaled CO.

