## Discussion

Focus on patient safety during the treatment process is a crucial aspect of the effective operation of healthcare systems globally. Undesirable pharmacological interactions have the potential to elevate a drug’s toxicity or diminish its effectiveness (34). Smoking is a cross-cutting problem in the medical field, and various specialists are seeking a valid, safe, effective, handy, and low-cost treatment for the cessation of cigarette smoking, including for inpatients. In fact, the majority of hospitalized smokers present co-morbid conditions, such as smoking-related diseases. For this population, smoking cessation is often mandatory, and physicians need safe and effective treatment options to reduce withdrawal symptoms and prevent relapse after discharge.

During hospitalization, treating withdrawal symptoms in smokers is essential. The ideal pharmacological treatment for smoking cessation in hospitalized patients with co-morbid conditions, who are often on polypharmacotherapy, should be handy, effective, safe, and well-tolerated in order to prevent further compromising their health. The following are predisposing factors for drug-related AE occurrence: advanced age, multiple morbidity, and polypharmacotherapy. It is important to consider that in wealthy countries, approximately 30–40% of those over 65 years of age take 5 or more drugs, and 12% use 10 or more medications (34).

Evidence about CYT’s pharmacokinetic profile suggests no or few drug interactions. For this reason, CYT could be considered a safe option for hospitalized smokers, who are often assuming concomitant therapies. Despite this, there is a lack of evidence in the literature about CYT’s safety profile in the hospitalized population.

For these reasons, safety assessment is a primary objective in the CITOSP protocol.

For CYT to be truly effective, following the adequate dosing schedule without interruption is critical. For these reasons, patient compliance and efficacy are the secondary objectives of the CITOSP protocol.

In 2021, the recall of CHAMPIX® (varenicline) from the market by Pfizer Inc. due to the presence of the impurity, N-nitroso-varenicline, a probable human carcinogen, above the acceptable daily intake limit, resulted in further shortages of CHAMPIX®, reducing therapeutic alternatives to NRT for smoking cessation (35).

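### Quit day is fixed as the first capsule day and earlier stopping is only partly recorded, so early abstinence, chiefly the 15-day figure at day 7, mixes new and prior quitters

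*Protocol article*

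**What the plan says.** The protocol article describes the smoking status of participants in three ways:

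- Inclusion criteria: "adults ≥18 years old admitted to IUHVR participating wards with a history of smoking and interested in quitting".
- Participant recruitment: "ward staff will refer all current smokers interested in quitting smoking to the CM".
- Study design: "observational prospective investigation involving smoking patients admitted to IUHVR and treated with CYT for smoking cessation".

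Participant recruitment also says that inclusion is decided on the predefined criteria, so the text under Inclusion criteria is the formal rule.

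Quit day (QD) is tied to treatment: "On the first day of therapy, all participants will be instructed to abstain from smoking and to quit completely (quit day, QD". The visit list under Visits and follow-ups adds a second meaning: "QD (first day of abstinence): start of integrated therapeutic plan with CYT".

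At visit 0 the listed smoking items include "efforts to quit smoking (number of times, date of last attempt, and use of some drugs to quit smoking" and "Smoking Status: average amount of cigarettes smoked in the last month, average cigarettes for the year", with age at first cigarette, the dependence score and use of other nicotine products. No date of last cigarette is listed. Table 1 first ticks exhaled CO at visit 1.

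Efficacy is a secondary objective. It is measured as self-reported 7-day and 15-day PPA at every timepoint, including visit 1 at day 7. Logistic models for relapse follow at day 25 and at 12 months.

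**The concern.** The first day of therapy and the first day of abstinence are the same day only if every participant smokes until the first capsule. In an inpatient study that is doubtful. The Discussion says of hospitalized smokers: "For this population, smoking cessation is often mandatory". A patient may stop on admission, be referred, consent, and start capsules later.

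Such a patient has already gone some days without smoking and without cytisine, yet is timed and reported as someone who quit on day 1. The study has one arm, so no comparison group carries the same mixture. A reader would take the early abstinence percentages as results of quitting with cytisine, when part of them may describe abstinence that came first. If the date of stopping is not recorded around quit day, it can later be recovered only by recall.

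**Working it through.** **1. Eligibility.** A history of smoking does not by itself require smoking now; the referral wording does. Neither gives a time since last cigarette. Read together, they make long-term ex-smokers unlikely but leave open the patient who stopped around admission.

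**2. What the listed baseline data can show.** The date of last quit attempt will identify some prior quitters. A stop imposed by the ward need not be recorded as an attempt. The last-month average is a blunt tool: five smoke-free days (an assumed figure) leave 25/30 of the usual consumption, a fall of one sixth, which lighter smoking would produce equally well.

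**3. Where each PPA window opens.** Start of window relative to QD = visit day − window length. Visit days come from Visits and follow-ups.

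| Visit | 7-day window opens | 15-day window opens |
|---|---|---|
| Visit 1, day 7 | 7 − 7 = 0 | 7 − 15 = −8 |
| Visit 2, day 25 | 25 − 7 = 18 | 25 − 15 = 10 |
| Months 3, 6, 12 | after QD | after QD |

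If QD is counted as day 1, as in the dosing table, the visit 1 entries move one day earlier, to −1 and −9. Either way, only the 15-day window at visit 1 lies largely before treatment.

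**4. Consequence for 15-day PPA at visit 1.** Let f be the share who stopped about 8 days or more before QD, and b the share of these still abstinent at day 7. Patients who smoked up to QD contribute zero if they report accurately:

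PPA = (1 − f) × 0 + f × b = f × b, which cannot exceed f.

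No abstinence rate need be assumed for this. The figure counts pre-treatment quitters only, and a patient who quits perfectly on day 1 scores as a failure.

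**5. Other PPA figures.** Let f now be the share already abstinent at QD, a the PPA in those smoking up to QD, and b the PPA in those already abstinent:

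PPA = (1 − f) × a + f × b.

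The protocol gives none of these, so the values below are assumptions.

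| Assumed a and b | f = 10% | f = 30% | f = 50% |
|---|---|---|---|
| Early: 40%, 60% | 42% | 46% | 50% |
| 12 months: 15%, 25% | 16% | 18% | 20% |
| 12 months: 15%, 15% | 15% | 15% | 15% |

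A wider early contrast, a = 40% and b = 80%, gives 0.8 × 40 + 0.2 × 80 = 48% at f = 20% and 0.6 × 40 + 0.4 × 80 = 56% at f = 40%. The last row of the table shows the condition: inflation needs both f > 0 and b > a at that timepoint.

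**6. The plan's own sample size.** The smallest n whose exact (Clopper–Pearson) 95% interval at 20% incidence is no wider than 10 points is 264 (15.3% to 25.3%), which matches the stated number. It rests on adverse event incidence alone, so nothing above changes it.

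**The case against.** There is a fair case on the other side.

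- **The population is described as smokers throughout.** Interest in quitting also implies someone who has not yet quit. This stands, and it confines the gap to recent stopping around admission. A reader might infer that former smokers are enrolled freely; the referral rule does not support that.
- **No interval from admission to visit 0, or from visit 0 to the first capsule, is given.** The Discussion sentence may mean medically necessary rather than already achieved. This stands: the share of prior quitters is unknown and could be small.
- **The article condenses a fuller protocol.** Co-adjuvants and concomitant medication are said to be recorded at each visit, yet neither has a row in Table 1, so the published lists are not the whole case report form. A last-cigarette item may exist. This weakens any claim that the information is absent, but not the mismatch in eligibility or the window arithmetic.
- **A reader might infer that abstinence is inflated at every timepoint, including 12 months.** The protocol does not support this. PPA looks back only 7 or 15 days, so stopping shortly before day 1 does not itself count as success at months 3, 6 or 12.
- **A reader might infer that the safety results are distorted too.** The plan reports cumulative incidence to day 25 and to 12 months, not events by stage of withdrawal, so this is speculative.
- **Efficacy is secondary and descriptive, without a comparator.** True, and it limits the weight of the point. The percentages will still be reported under efficacy and should describe a defined group.

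**Conclusion.** The concern holds in a limited form. The two eligibility statements disagree, and quit day is assumed rather than observed. The listed baseline items only partly separate patients who quit on day 1 from those who had stopped before.

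The firm consequence is at visit 1: 15-day PPA there cannot be met by anyone who smoked up to quit day. This follows from the visit day and the window length, assuming only accurate self-report. For 7-day PPA at visit 1 and all abstinence figures from day 25 onward, inflation is possible but depends on prior quitters being present and doing better; its size cannot be computed from the protocol. The primary safety endpoint and the sample size of 264/300 stand. The change is worth making because it is cheap now and hard to make up later.

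**What to change.** 1. Word the inclusion criterion and the referral rule alike, so that both refer to current smokers, and say what that means for someone already admitted.
2. Record the date of last cigarette at visit 0 and again on quit day, or confirm that the full case report form already does so.
3. Report PPA separately for patients smoking up to quit day and those already abstinent.
4. Do not report 15-day PPA at visit 1 as an efficacy result. From day 25 onward the window lies wholly after quit day and can be kept.
5. Add days abstinent before quit day as a candidate predictor in the relapse models.

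A limit on time from last cigarette to admission would not help, because it misses patients who stop on admission. An additional CO reading at baseline is not needed.

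The cost is one eCRF item at two existing contacts, one split in the abstinence table and a wording change. The abstinence figure for true day-1 quitters may come out lower and will rest on fewer patients.

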#### Exclusion criteria

Patients who do not fit all of the requirements mentioned above, those who have any contraindications for the use of CYT, such as reported hypersensitivity to CYT, pheochromocytoma, malignant hypertension, unstable angina, will be excluded from the study, as will women who are breastfeeding, pregnant or likely to become pregnant during CYT treatment and are not willing to use an effective form of contraception.

Until the baseline visit, the use of other forms of nicotine delivery, such as electronic cigarettes, in combination with industrial cigarettes, will not be an exclusion criterion. However, the use of nicotine-containing products as smoking cessation medications (e.g., NRTs) starting from the QD will cause the exclusion of participants from the study, while the use of co-adjuvants for smoking cessation (e.g., electronic cigarettes without nicotine, Nirdosh®) will be allowed, according to clinical practice, and will be recorded in eCRF at each visit.

Because CYT is eliminated through urine unmodified, patients with chronic kidney failure will be closely monitored but not excluded from the trial. Patients in stage IV or V, with glomerular filtration rate (GFR) < 29 mL/min, will receive CYT treatment with halved dosage; patients in stage III, with GFR between 30 and 59 mL/min, will receive standard CYT treatment, but close patient monitoring will be performed.

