### Visits and follow-ups

All participants will be followed up for a period of 12 months after treatment initiation (Figure 1).

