### Sample size and statistical analysis

Assuming an overall incidence of all AEs and ADRs equal to 20% as reported by Hajek et al. (28), 264 subjects will be needed to produce a bilateral confidence interval of 95% with an amplitude of 10%. This number will be increased to 300 subjects to compensate for a potential loss of 14% of subjects during the 12-month follow-up. To recruit 300 subjects, it will take 36 months. The total duration of the study will be 4 years.

All variables recorded in the study will be presented using the plus descriptive statistic appropriate to their nature. Continuous variables will be presented with mean and standard deviation with median and interquartile distance based on their distribution; ordinal and categorical variables will be presented with frequency and percentage.

To assess the safety of treatment with CYT, the incidence of AEs and ADRs will be evaluated, with respective 95% confidence intervals (CIs) up to the end of treatment (day 25) and up to 12 months from the start of the treatment (quit day). The percentage of subjects will be calculated to assess the compliance of patients with CYT treatment who respected their dosage schedule with the respective 95% CI.

To evaluate the efficacy of CYT treatment, the percentage of subjects who reported abstinence in the previous 7 days and 15 days (7-day PPA and 15-day PPA) before each study timepoint will be calculated. For in-person visits and follow-ups, the PPA will be biochemically verified through exhaled CO measurement.

The efficacy will also be studied at a multivariate level to assess whether the positive/negative outcome of the treatment is associated with certain demographic and/or clinical factors. For this type of analysis, they will construct logistic regression models by setting the (yes/no) relapse evaluated as dependent variables according to the reported and objective efficacy criteria at the end of treatment (25^th^ day from the start of treatment) and 12 months from the start of treatment. The independent variables will be chosen based on the assumptions of experimenters on possible predictors of efficacy, including the result of the FTND, the ward, the primary cause of admission, sex, age, education, occupation, age in which the person started smoking, and number of previous smoking cessation attempts.

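### Excluding participants from the study for NRT use after quit day selects on a post-treatment event, contradicts the 12-month follow-up of all participants, and loses adverse-event and abstinence data

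*Protocol article*

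**What the plan says.** The Exclusion criteria section of the protocol article contains a rule that acts during the study: "the use of nicotine-containing products as smoking cessation medications (e.g., NRTs) starting from the QD will cause the exclusion of participants from the study". It gives no date after which the rule lapses. The same paragraph allows nicotine-free aids and has them recorded in the eCRF at each visit.

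Other sections bear on this:

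- **Participant recruitment** makes quit day the first day of therapy. It also says: "Any participant who meets the exclusion criteria will not be recruited".
- **Visits and follow-ups** says: "All participants will be followed up for a period of 12 months after treatment initiation". Setting and participants likewise promises a full year of follow-up.
- **Clinical endpoints** defines relapse by cigarettes smoked or by exhaled CO. NRT use is not itself a relapse.
- **Sample size and statistical analysis** reports AE and ADR incidence with 95% confidence intervals to day 25 and to 12 months, and for efficacy "the percentage of subjects who reported abstinence in the previous 7 days and 15 days" before each timepoint. It does not say whether participants excluded for NRT use stay in these percentages.

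**The concern.** An exclusion criterion normally works before enrolment. This one is triggered by something that happens after the first capsule and is plausibly related to outcome: a patient may turn to NRT because withdrawal is not controlled, because cytisine was stopped, or after a relapse. A patient who completes 25 days of cytisine and uses NRT months later would still be excluded, despite complete on-treatment safety data.

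Two things are at stake. First, AEs, self-reported abstinence and CO readings after the exclusion are not collected, and no later analysis plan can restore them. Second, if these patients also leave the denominators, the reported percentages describe a set selected after treatment began and not the treated inpatients named in the objectives.

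**Working it through.** **1. The texts side by side.** The trigger in the Exclusion criteria can occur only from day 1 of therapy. The rule in Participant recruitment, that patients meeting an exclusion criterion are not recruited, cannot be applied to it. Exclusion from the study and 12 months of follow-up for all participants cannot both be followed for the same patient.

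**2. The plan's own figure.** At an assumed incidence of 20%, the smallest n with an exact (Clopper-Pearson) 95% interval no wider than 10 points is 264 (width 9.99 points; 263 gives 10.01). The stated 264 is reproduced. The raised figure of 300 is close to 264 × 1.14 = 301. The sample size is not in dispute here.

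**3. Abstinence.** Let a be the true rate among all treated, q the share excluded for NRT use, and s the abstinence rate among those excluded. If they leave the denominator:

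reported rate = (a − q·s) / (1 − q)

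The documents give none of a, q or s, so all are assumed. With a = 30% and s = 0 the factor is 1/(1 − q):

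| q | reported |
|---|---|
| 5% | 0.30/0.95 = 31.6% |
| 10% | 0.30/0.90 = 33.3% |
| 20% | 0.30/0.80 = 37.5% |

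These are upper values. With s = 15% and q = 10%, the result is (0.30 − 0.015)/0.90 = 31.7%. If NRT users do better than the rest, the sign reverses: a = 20%, s = 30%, q = 20% gives (0.20 − 0.06)/0.80 = 17.5%.

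**4. AE incidence, excluded participants kept in the denominator but no longer followed.** Later first AEs are missed, so the 12-month figure can only be too low or correct. As an illustration, suppose their AE rate equals the overall 20% and every first AE falls after exclusion. The reported figure is then 0.20 × (1 − q) = 19%, 18% or 16% at q = 5%, 10% or 20%.

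**5. AE incidence, excluded participants removed entirely.** Let RR be the AE rate in excluded relative to retained participants, with true overall incidence 20% (the protocol's planning value):

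retained-set incidence = 0.20 / ((1 − q) + q·RR)

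| q | RR = 2 | RR = 1 | RR = 0.5 |
|---|---|---|---|
| 5% | 19.0% | 20.0% | 20.5% |
| 10% | 18.2% | 20.0% | 21.1% |
| 20% | 16.7% | 20.0% | 22.2% |
| 30% | 15.4% | 20.0% | 23.5% |

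The sign depends on RR, which the documents do not give.

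**The case against.** The strongest reply is that removal from the analysis is inferred. The article does not state the denominators, does not say that data recorded before exclusion are discarded, and may leave analysis sets to a full protocol or SAP that is not shown. That stands as far as the denominators go, and it is why the figures above are conditional. It does not answer the main point: the article states a rule that ends participation, and a SAP can only analyse data that were collected.

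Three stronger readings are tempting, and the documents do not support them:

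- **That the rule makes both safety and abstinence look better.** For safety this would require NRT users to have more AEs than the rest, or AEs after exclusion to be missed while they stay in the denominator. The documents establish neither, and the bias under full removal can go either way.
- **That only patients for whom cytisine worked and was tolerated remain.** Patients who return to cigarettes without NRT stay in; visits 1, 3, 4 and 5 record their cigarette counts. Patients with AEs who do not take NRT also stay.
- **That the sample size makes no allowance for these exclusions.** The 14% is described as potential loss during the 12-month follow-up. That wording does not mention NRT exclusions, but it does not rule them out.

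Handling of participants lost for other reasons is a separate matter and is not part of this point.

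**Conclusion.** The point holds as a defect in a stated rule. NRT use from quit day leads to exclusion on a post-treatment, plausibly outcome-related event, in conflict with three other sections, and data on treated participants are lost if the rule is followed.

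The size cannot be fixed from the documents. Abstinence is inflated only if NRT users leave the denominator and are abstinent less often than the rest. The factor is at most 1/(1 − q), which takes an assumed 30% to between 31.6% and 37.5% for q of 5% to 20%. The 12-month AE incidence, part of the primary analysis, is incomplete. It is understated if excluded participants remain in the denominator unfollowed and have their first AE later. If they are removed, it could lie between about 15.4% and 23.5% for a true 20%, with q up to 30% and rate ratios of 2 to 0.5. No claim is made that safety is biased in a particular direction.

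**What to change.** Reconcile the Exclusion criteria with Setting and participants, Participant recruitment, and Visits and follow-ups, so that NRT use after quit day ends neither study follow-up nor inclusion in the analyses. Specifically:

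- Record NRT use, with dates, at every visit to month 12. Nicotine-free aids are already recorded in the eCRF at each visit, and concomitant medication during treatment is already documented.
- Keep everyone who took at least one capsule in the safety denominator, with AE collection continued.
- Keep NRT users in the abstinence percentages and relapse models by their smoking status. Add a sensitivity analysis counting them as failures, and keep an analysis without NRT users as secondary.

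This concerns data collection and analysis only and takes no position on whether NRT should be used. The cost is a wording amendment and the completion of visits already scheduled for these participants. The reported abstinence rate may be slightly less favourable.
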